### Intervention group: Health*e*Steps™ Program

There are three phases to the intervention: an *active phase* that encompasses the first six months, a *maintenance phase I* for the next six months, and finally a *maintenance phase II,* which is the last six months of the trial.

#### Active phase (months 0–6)

Participants assigned to the intervention group will start the Health*e*Steps™ program within three weeks of completing their baseline measurement session. Participants will receive a handbook that contains documents to help them track their progress throughout the program and will be given a pedometer to use to track their PA. The research team chose to utilize pedometers to measure step counts as they are inexpensive, easy to use, and easily interpreted by the participant and research team [35]. In total, participants will receive four bi-monthly in-person coaching sessions (occurring at months 0, 2, 4, and 6) with a Health*e*Steps™ coach who will be trained on how to create an action plan with the participant to help them work towards achieving their lifestyle prescriptions. Strategies for setting lifestyle prescriptions are based on S.M.A.R.T. goal setting principles (specific, measurable, attainable, realistic, and timely for the participant), as goal setting has been found to produce positive behaviour change in adults [36]. The lifestyle prescriptions and supports are as follows:
*Exercise Prescription:* The exercise prescription focuses on making incremental changes in the amount of time the participant engages in moderate to vigorous activity or the amount of time they exercise within their target heart rate zone, up to the recommended 150 min/week. At each program session, participants will complete a sub-maximal fitness test, the Step Test and Exercise Prescription tool (STEP™ Test) [37]. Based on their fitness score from this test (i.e., predicted maximal oxygen uptake, VO2max), participants will receive an exercise prescription with a personalized target heart rate (65–85% of estimated maximum heart rate) for exercise. Coaches will then encourage participants to exercise at their training heart rate and/or at a rating of 5–8 on the 10-point modified Borg Rating of Perceived Exertion scale during aerobic activities [38]. The Health*e*Steps™ coach will collaborate with the participant to set a weekly target of exercise minutes that includes frequency, duration, and type of exercise to facilitate achievement of their exercise prescription.
*Physical Activity Prescription:* The PA prescription focuses on making incremental changes to the participants’ daily step count to reach the recommended 10,000 steps per day. This requires setting a baseline step count, which for coaching session 1 will be the participants’ step count recorded during the baseline measurement session. For sessions 2 to 4, the prescription will be based on steps logged in the participants’ handbook completed between sessions. If the participant did not track their step counts between coaching sessions, the coach and participant will work together to develop a reasonable target step count to set a new PA prescription.
*Healthy Eating Prescription:* Using Eating Well with Canada’s Food Guide, participants will work with their coach to determine their current daily intake from each food group, their water intake, and consumption of a healthy balanced breakfast. The healthy eating goal is set through increasing or decreasing a serving in one of the food groups to better meet the recommendations (i.e., increasing one serving of vegetables and fruit or decreasing a serving of meats and alternatives), increasing water intake and increasing the number of days the participant consumes a healthy balanced breakfast.
*Access to the HealtheSteps™ eHealth Technology Suite:* Tyze Personal Networks [39] and Sykes [40] phone coaching will provide participants with support in between coaching sessions and will be available during the *maintenance phase I* until the 12 month assessments are complete. Tyze Personal Networks is a web-based platform that provides an exclusive network for connecting with central research staff, coaches, and other participants through private chat services and posting information on a CareWall (similar to a Facebook wall). Sykes provides phone coaching services to support participants in-between coaching sessions and during *maintenance phase I*. Sykes CareCoaches® are trained in the Health*e*Steps™ protocol and act similarly to the Health*e*Steps™ coach, working with participants to address any challenges they may be experiencing and providing encouragement for them to meet their goals.Participants will be encouraged to seek out publicly available healthy living supports, such as the Health*e*Steps™ website (http://healthesteps.ca/) for healthy living resources and the Health*e*Steps™ and eaTracker smartphone apps. The Health*e*Steps™ app (available for free download on Apple and Android devices) has a built-in fitness test and heart rate monitor. Additionally, through the help of a virtual coach, the app provides personalized prescriptions, goals, and tracking options to help participants maintain their goals developed with their in-person coach. The eaTracker allows participants to monitor food and activity choices, analyze recipes, and create meal plans. These publicly available supports are available to participants throughout the active and maintenance phases as well as beyond the trial period.

Between coaching sessions, participants will be expected to self-direct their healthy living activities, using healthy living resources (Eating Well with Canada’s Food Guide and Canadian Physical Activity Guidelines) and *e*Health technology support options.

#### Maintenance phase I (months 6–12)

Participants will no longer have in-person coaching sessions, but will have access to the full suite of *e*Health technology support tools.

#### Maintenance phase II (months 12–18)

Participants will no longer have access to the online Tyze Personal Networks, and Sykes phone coaching services, but will still have access to the publicly available resources, including the HealtheSteps™ and eaTracker Smartphone apps, and the Health*e*Steps™ website.

### Comparator group (wait-list control)

This group will continue with usual activities without intervention from the study team for the first 6-month period. After the 6 month measurement sessions are completed, participants allocated to this group will be given the opportunity to start the 6-month Health*e*Steps™ program.

### Data collection

#### Outcome evaluation

The outcome measures will be taken at baseline and 6 months in both groups, and then again at 12 and 18 months in the intervention group only (see Table 1). Home visits will be conducted when participants are unable to attend follow-up measurement sessions at the sites to increase participant retention throughout the long-term follow-up. Data sources will include self-reported PA, participant demographics, clinical measures, and the completion of health related information and questionnaires (See Table 2).

**Table 1 Tab1:** Screening and measurement sessions schedule

Measurement	Screening	Baseline	6-month	12-month (Intervention Group only)	18-month (Intervention Group only)
*Screening & Eligibility Measures*					
Participant Self-Reports at Screening	X				
Pre-Randomization ID #	X				
Letter of Information & Consent Form	X			X	
PAR-Q	X				
Health Care Provider Clearance Form	X				
Eligibility Form	X				
Group Allocation		X^a^			
Participant ID#		X^a^			
*Baseline Health Information*					
Demographics & Health Related Information		X			
*Clinical Measures*					
Age	X	X^b^			
Height	X	X^b^	X^b^	X^b^	X^b^
Weight	X	X^b^	X	X	X
Body Mass Index	X	X^b^	X	X	X
Waist Circumference		X	X	X	X
Blood Pressure		X	X	X	X
*Self-Reported Physical Activity*					
Average Steps/day (Step Count Outcome Tracking Form)		X	X	X	X
International Physical Activity Questionnaire		X	X	X	X
*Self-Reported Eating*					
Modified DINE		X	X	X	X
Starting the Conversation		X	X	X	X
*Health-Related Quality of Life*					
EQ-5D-3 L		X	X	X	X

^a^Occurs at Randomization & Allocation Session

^b^Use number recorded at Screening Session

**Table 2 Tab2:** Data collection & measurement protocol

Outcome Measure	Equipment required	Protocol
*Self-Reported Physical Activity*		
Average steps/day	Pedometer (Yamax Digiwalker SW-200 with security strap)	• Participants wear pedometers during waking hours for a 7-day period (putting pedometer on upon waking and removing immediately before sleeping), but not during showering/bathing • Participants are asked to wear the pedometer at the waist, centered over their most dominant foot • Participants record the number of steps completed each day on a paper-based tracking form
Total physical activity (MET-min/week^a^)	International Physical Activity Questionnaire (IPAQ) – Short Form [43]	• Self-completed paper‐based questionnaire • Participants recall information on vigorous activities, moderate activities, walking, and sitting • Sedentary time is measured with a single question (minutes spent sitting on a typical week day) • The IPAQ provides guidelines for data processing and score creation
Time spent in sedentary activity (min/day)		
*Clinical Measurements*		
Weight (kg and percentage of baseline weight)	Digital Weight Scale (Tanita HD 351)	• Light clothing, no shoes and empty pockets • Blinded assessor post-baseline in private area
Body mass index (kg/m2)	Digital weight scale (Tanita HD‐351) Portable stadiometer (seca 213)	• BMI calculated using the participant’s objectively measured height and weight • Height measured without shoes
Waist circumference (cm)	Tape measure	• Follows protocol outlined by the Heart and Stroke Foundation of Canada [44] • Two measurements taken to record an average; if measurements differ by more than 5 mm, a third measurement is taken and used in the average
Systolic Blood Pressure (mmHg)	Digital BP monitor (BP Tru BPM-100)	• Participants sit quietly for 5 min prior to the first measurement; 3 measurements will be taken, 2 min apart. The first one is discarded, and the average of the last two is recorded. • Feet flat on the floor, arm free of clothing, cuff at the level of heart and arm resting, same arm used (left arm preferred), no talking
Diastolic Blood Pressure (mmHg)		
*Self-Reported Eating*		
Fatty Food Score	Modified version of the Dietary Instrument for Nutrition Education (DINE) [46]	• Self-completed paper-based questionnaire • Participants recall eating habits over the last 7 days • Methods published by FFIT will be followed to calculate a fatty food score (possible range 8–68) and sugary food score (possible range 3–16), with higher scores indicative of higher consumption • Fruit and vegetable consumption is measured with a single question
Sugary Food Score		
Fruit and vegetable consumption		
Total healthful eating score	Starting the Conversation [45]	• Self-completed paper-based questionnaire • Designed for dietary assessment and intervention in a clinical setting • Participants recall eating habits over the past few months (on average) on 8 different items • A total healthful eating score (possible range 0–16) is calculated, whereby a lower score indicates a more healthful diet
*Health-Related Quality of Life*		
Self-Rated Health [visual analog scale (VAS) score]	European Quality of Life 5 Dimensions Questionnaire - 3 Level Version (EQ‐5D- 3 L) [48]	• Self-completed paper-based questionnaire • For purposes of this study, the VAS score will be used to assess current state of health on a scale from 0 (worst imaginable state of health) to 100 (best imaginable state of health)

^a^METs (metabolic equivalents) are multiples of the resting metabolic rate; MET-minute = multiplying the MET score of an activity by the minutes performed

Average steps per day, measured using Yamax Digiwalker SW-200 pedometers and self-reported by participants using a 7-day paper log [41, 42] (at least 3 days of logging required).Total physical activity (Metabolic Equivalent (MET)-minutes/week) measured using the International Physical Activity Questionnaire (IPAQ) Short Form [43]; and time spent in sedentary activity (minutes spent sitting on a typical week day) measured with the IPAQ.Objectively-measured clinical characteristics: weight (using Tanita HD 351 Digital Weight Scale; kg and % of baseline weight), Body Mass Index (BMI, calculated from weight and height in kg/m^2^), waist circumference (cm) [44], and resting systolic blood pressure (BP) and diastolic BP (using BP Tru BPM-100; mmHg).Self-reported eating: healthful eating score, measured using Starting the Conversation (STC) questionnaire [45]; fatty food score, sugary food score, as well as fruit and vegetable consumption, measured using a modified version of the Dietary Instrument for Nutrition Education (DINE) [46] and following scoring outlined by Hunt and colleagues [47].Self-rated health measured using the European Quality of Life – 5 Dimensions – 3 Levels (EQ-5D-3 L) visual analog scale (VAS) score [48, 49].

#### Process evaluation

Data collection for the process evaluation will also be collected during baseline, 6, 12, and 18 month measurement sessions (see Table 3). Information about how participants heard about the program, demographic information, interviews with coaches, participants and program non-completers, questionnaires completed by participants, and participant compliance and retention will inform the acceptability of the intervention.

**Table 3 Tab3:** Data sources to address process measures

Process measures	Data sources
Program Reach	Participant Screening and Baseline Demographics
	12-Month Participant Program Questionnaire
	12-Month Participant Interview
Reasons Participants Stayed With/Opted Out of the Program	Interviewer-Guided Participant Feedback Questionnaires
	Program Compliance Records
	Non-Completer Telephone Interviews
	12-Month Participant Program Questionnaire
	12-Month Participant Interview
Extent to which Coaches Delivered Health*e*Steps as Designed	Coach Interviews
Participants’ Experience Taking Part in Health*e*Steps	Interviewer-Guided Participant Feedback Questionnaires
	12-Month Participant Program Questionnaire
	12-Month Participant Interview
	18-Month Participant Program Questionnaire
Coaches’ Experience of Delivering Health*e*Steps	Coach Interviews
Participants’ Experience Maintaining Lifestyle Changes	12-Month Participant Program Questionnaire
	12-Month Participant Interview
	18-Month Participant Program Questionnaire

**At screening and baseline**, participants will be asked how they heard about the study and demographic information will be taken.

**At 6 months**, participants who completed the Health*e*Steps™ program will be asked to complete an Interviewer-Guided Program Feedback Questionnaire; in order to capture all relevant information about the program, participants will be guided through the feedback forms by a trained interviewer, in-person or by phone. Participants will be asked about how useful they found different program components, benefits they may have experienced through the program, helpful methods for keeping on track with their healthy lifestyle goals, barriers and challenges in maintaining their goals, and experience using the *e*Health technology suite.

Health*e*Steps™ coaches will have the opportunity to express their thoughts on delivering the Health*e*Steps™ program through an interview conducted by a trained interviewer in-person or through the phone. Interviews will be kept anonymous with questions exploring their experience delivering the Health*e*Steps™ program to participants, preparedness for program delivery, effectiveness of different program components and suggestions to improve the different program components. Prior to these interviews, coaches will be asked to read through a letter of information and sign a consent form allowing the interviewer to audio record the interview for more thorough analysis.

Participants who are enrolled in the study but do not complete any coaching sessions or complete only one coaching session, half of the coaching sessions or do not attend sessions 3 or 4, will be defined as non-completers. Program non-completers will be asked in-person or via phone, a series of questions about why they joined the Health*e*Steps™ program, barriers for participating in the program, and changes they may have made during their enrollment in the program.

All data sources at 6 months will be kept anonymous in order to encourage open and honest answers and prevent bias during the data analysis stage.

**At 12 months**, participants will be asked to complete a 12-month Program Questionnaire detailing what they have been able to maintain throughout *maintenance period I,* and whether they used the *e*Health technology support tools. Participants will also be asked to participate in an interview exploring their experience maintaining their health behaviour changes 6 months after the *active phase*. Questions will explore their overall experience with the program; their experience maintaining the changes in exercise, PA levels, and eating habits; the *e*Health technology support tools; and impact their participation in the program may have had on friends and family.

**At 18 months**, participants will be asked to complete a final questionnaire about their experience maintaining healthy lifestyle changes one year after completion of the active phase. Questions will also focus on support systems they may have used to maintain their lifestyle changes as Tyze Personal Networks and Sykes Phone Coaching supports ended at 12 months.

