### Adverse events

Participants will be given information at baseline on reporting adverse events to the central research team throughout their participation in the study. Adverse events are described as any injury or newly diagnosed health condition (i.e., high blood pressure, diabetes) that occurs while a participant is enrolled in the Health*e*Steps™ study, whether or not it is related to their participation in the Health*e*Steps™ program. At each coaching session, participants in both the intervention and comparator groups will be asked about any adverse events they may have experienced while they were enrolled in the Health*e*Steps™ study, and whether it was related to their participation in the program. The adverse events will be reviewed by the lead study physician and if necessary, refer participants for appropriate event follow-up. The outcome of adverse events will be followed until the end of the study.

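### The only scheduled adverse-event question is asked at coaching sessions, so it ends when a participant stops attending, and the 6-month anonymity rule has no safety exception

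*Protocol article*

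**What the plan says.** All references are to the Protocol article.

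**Adverse events** defines an event as any injury or new diagnosis during enrolment, related to the program or not. It gives two routes of collection:
- Passive: "Participants will be given information at baseline on reporting adverse events to the central research team throughout their participation in the study".
- Active: "At each coaching session, participants in both the intervention and comparator groups will be asked about any adverse events they may have experienced".

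It then sets the handling: "The adverse events will be reviewed by the lead study physician and if necessary, refer participants for appropriate event follow-up", and "The outcome of adverse events will be followed until the end of the study".

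**Active phase** fixes the coaching sessions as "occurring at months 0, 2, 4, and 6". **Maintenance phase I** ends them: "Participants will no longer have in-person coaching sessions, but will have access to the full suite of" eHealth tools.

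**Process evaluation** defines non-completers by missed coaching sessions. They are to be asked, in person or by phone, why they joined, and about "barriers for participating in the program, and changes they may have made during their enrollment in the program". The 6-month feedback questionnaire goes to those who completed the program. The 6-month description closes with "All data sources at 6 months will be kept anonymous in order to encourage open and honest answers", and gives avoiding bias at analysis as a second reason.

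**Table 1** lists no adverse-event item at the baseline, 6-, 12- or 18-month sessions.

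**The concern.** The definition of an adverse event covers everyone enrolled, but direct questioning covers only those who come to coaching. The program prescribes exercise at a target heart rate and repeats a sub-maximal fitness test at each session, in at-risk adults up to age 85. It is a reasonable inference, though not something the article states, that injury or illness will be among the reasons some people stop. If so, the events that end attendance are the ones least likely to be asked about, and the intervention group's recorded harms understate the true ones.

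The non-completer interview is where such an event would naturally come up, as a barrier. Yet it has no stated safety question, and its data fall under an anonymity rule that, read literally, gives the physician nobody to review, refer or follow.

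**Working it through.** **1. The plan's own figure.** The article's one computed design figure is the sample size. For an effect size of 0.65, two-sided 0.05 and 80% power, 38 per group reproduces (power 0.809 by the normal approximation, 0.799 by the noncentral t). With 30% dropout, 38 / 0.70 = 54.3, rounded up to 55 per group, or 110 in total. This agrees with the article. The present point does not depend on it.

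**2. Who is asked, and when.** From the Adverse events and Active phase sections, for an intervention participant:

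| Attendance | Direct questions asked (of 4) | Last asked | Part of months 0–6 with no later question |
|---|---|---|---|
| No session | 0 | never | all 6 months |
| Session 1 only | 1 | month 0 | all 6 months |
| Sessions 1 and 2 | 2 | month 2 | 6 − 2 = 4 months |
| All four | 4 | month 6 | none |

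Someone who attends only session 1 is asked once, at the start of the program, before there has been much exposure to it. After month 6 nobody in this group has a coaching session, so the dependence on attendance concerns the active phase.

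**3. The two rules side by side.** Physician review, referral if needed and follow-up of the outcome each require knowing whose event it is. The anonymity sentence covers all 6-month sources and names no exception. The non-completer interview is described in the same 6-month block, so it is covered. The article does not say how an injury mentioned there would be recorded or passed on.

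**4. Size.** Let p be the share of the intervention group that stops coaching, r their risk of an event, and c the share of their events still captured by self-report or other contact. If all other participants' events are recorded, the shortfall in the group's recorded risk is p × r × (1 − c). The article gives none of p, r or c.

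An illustration follows; every input is an assumption. It uses the 30% dropout allowance as a stand-in for non-completion (55 × 0.30 = 16.5, taken as 17), a risk of 10% in the other 38 and 30% in the 17:
- True risk: (38 × 0.10 + 17 × 0.30) / 55 = 8.9 / 55 = 16%.
- Half of the non-completers' events captured: (3.8 + 2.55) / 55 = 6.35 / 55 = 12%.
- None captured: 3.8 / 55 = 7%. This is the extreme case.
- All captured: no shortfall.

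With an equal risk of 10% in both and none captured, 5.5 / 55 = 10% would be recorded as 3.8 / 55 = 7%.

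**The case against.** **The self-report route.** It is open throughout participation, does not depend on coaching and feeds the same physician review. This stands. A reader might infer that an injury in a non-completer cannot reach the physician; the article does not support that. What remains is an inequality: attenders have self-report and direct questions, non-completers have self-report alone.

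**Anonymity as data handling.** The stated reasons are candour and unbiased analysis, and the interviewer contacts a known non-completer in person or by phone. The sentence may therefore govern storage and analysis only, and nothing expressly forbids passing an event on. This also stands, so the conflict is one of wording as written, not proof that review is impossible. The wording still needs reconciling, because staff who follow it literally would leave the event unlinked.

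**Other contacts.** Table 3 also lists compliance records and the 12-month questionnaire and interview as sources on opting out. Measurement sessions continue, with home visits. So the non-completer interview is not the only later contact. But the 12-month sources come six months later and are described as covering program experience and maintained changes, and no measurement session lists an adverse-event item.

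**Condensed article.** The interview guide may hold a safety question that the article does not show. That is fair for the missing question taken alone. It does not cover the two things the article does state: direct questioning tied to coaching sessions, and anonymity without an exception.

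**No planned analysis of harms.** The outcome analysis section plans no comparison of adverse-event risk. A reader might infer bias in favour of the intervention in a between-group comparison. The article does not support a direction: the comparator group has no coaching sessions in its first six months, so it would not be asked directly then either. The point concerns completeness of recording within the intervention group.

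**Conclusion.** The concern holds in a limited form. Followed as written, the plan collects harms less completely from intervention participants who stop coaching than from those who continue. Its anonymity statement also needs reconciling with its own rules on review, referral and follow-up.

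The direction, under-recording among those who stop, rests on one assumption: self-report without prompting captures fewer events than self-report plus direct questions. That harm is a cause of stopping is plausible but not documented. If it is, the loss falls on the most informative events.

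The size is unknown. The drop from 16% to 7% is an extreme illustration. It assumes both risks, treats planned dropout as coaching non-completion, and supposes that no event in a non-completer is recorded by any route, including at sessions attended before stopping. It should not be cited as an estimate. The change is worth making because it alters how events are collected, at very little cost.

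**What to change.** 1. In the Adverse events section, state that the standard adverse-event question is put to everyone who stops coaching, and place it in the planned non-completer interview. The 6-month measurement session could carry it as well, which would also reach people who decline the interview.
2. In the Process evaluation section, add one sentence of exception to the anonymity rule: any injury or new diagnosis mentioned in a 6-month source is recorded under the participant ID and handled as the Adverse events section sets out. Opinion answers stay anonymous.

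The cost is one question in a contact already planned and one sentence of text. The downside is that participants must be told beforehand that health events are not anonymous, which may make a few less forthcoming on that item.
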